### *4.2 Statistical analysis*

The effect of hydration (euhydrated/dehydrated) on the influence of fan use (on/off) for all outcomes will be assessed using a Linear Mixed Model analysis with Sidak post-hoc testing.

Specifically, we will use a restricted maximum likelihood (REML)-based linear mixed model, accounting for repeated measures, including a term for hydration status (euhydrated, dehydrated), a term for condition (no fan use, fan use), and interaction term between hydration status and condition. This model will be used to compare end-trial values in the primary outcome variables: rectal temperature, heart rate, and whole-body sweat rate, and the secondary outcome variables: thermal sensation, thermal discomfort and thirst. Any missing data will be handled under the Missing At Random (MAR) assumption without listwise deletion. This allows the retention of participants who have missing data in one or more conditions. All available data will be used in the estimation of fixed effects.

The significance threshold is set at  $P=0.05$ . SPSS Statistics (v29.0.1) will be used for all statistical analysis.

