### **3 - Methods**

#### *3.1 Study design*

A repeated measures (crossover) design study requiring all participants to complete one 5-day 'hydration baseline' period, followed by four 3-h passive heatwave exposures (counterbalanced using balanced Latin square design), two whilst well hydrated, two hypohydrated, both with and without an electric fan. Experimental trials will be separated by at least 96 h, and all preceded by a 24-h period of carefully prescribed fluid consumption that will ensure either euhydration or contribute to the development of moderate hypohydration. A crossover design was selected because the lower within-person variation in the human heat stress response compared to between individuals enables better statistical power for the detection of between-condition effects.

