##### Main experimental trials:

Following a 5-day hydration baseline, participants will be asked to complete four 3-h passive heatwave exposures (39°C, 50% relative humidity) with all trials separated by a minimum of 4 days, to eliminate any carryover effects, and completed within a 3-week span to ensure no discernible difference in heat acclimatization status. All experimental trials are scheduled to start at 0800 h, with participants twice asked to adhere to a 'high fluid intake' and twice to a 'low fluid intake' protocol in the 24 h leading up to the experimental visit. The aim of the high fluid intake protocol is to ensure the participant arrives well hydrated for their experimental

visit. Based on the work of Armstrong and Johnson (2018) detailing daily fluid requirements of men and women [17], female participants were asked to consume 1.8-2.1 L, and male participants 2.4-2.8 L of water throughout the day before their two euhydrated trials, as well as ~500 ml of water alongside a light meal in the 2 h leading up to the trial. The low fluid intake protocol requires participants to consume no water or any other drink during the 24 h leading up to their two hypohydrated trials, as well as the avoidance of food products with >75% water content, a protocol that has previously resulted in a 24-h body mass reduction of ~2% [18].

In advance of all experimental trials, participants will also be asked to abstain from caffeine and alcohol and to avoid strenuous physical exertion for 24 h. Additionally, participants will be asked to maintain a food diary throughout their first high and low fluid intake protocols and replicate them the second time they undergo each protocol.

The four experimental trials differ firstly in hydration status upon arrival and throughout (euhydrated or hypohydrated) and secondly via the employment of an electric fan, placed 1.5 m from the participant provided constant forced airflow of 2.5 m/s (measured 1.5 m away from the fan) throughout the exposure, equivalent to the high setting on a commercially available pedestal fan. The four experiment trials are therefore:

- (1) Euhydration, No-Fan (EUH-NF)
- (2) Euhydration, Fan (EUH-FAN)
- (3) Hypohydration, No-Fan (HYP-NF)
- (4) Hypohydration, Fan (HYP-FAN).

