## **4 - Statistics**

### *4.1 Sample size*

To complete this study, we plan to recruit at least 16 young healthy participants (non-smokers with no history or current respiratory, metabolic, and cardiovascular illness/disease, high blood pressure, or diabetes, and not currently on any medication. Male/female participants between the ages of 18 and 40 will be recruited. The number of participants was selected by performing a power calculation using an  $\alpha$  of 0.05, a  $\beta$  of 0.1, an effect size of 0.78 calculated from the differences in change in rectal temperature between euhydrated and mildly (1.9% total body weight) dehydrated individuals across a three hour heatwave simulation [14].

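### The four exposures are counterbalanced by Latin square, but the mixed model has no visit term; if responses drift by more than about 0.5 within-person SD, the interaction test loses power

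*Protocol*

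**What the plan says.** Protocol section 3.1 describes a crossover with "four 3-h passive heatwave exposures (counterbalanced using balanced Latin square design". Each participant therefore has a known visit position, 1 to 4, for each condition.

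Under the heading on the main experimental trials, two scheduling rules are given. Visits are spaced "with all trials separated by a minimum of 4 days, to eliminate any carryover effects", and all four are "completed within a 3-week span to ensure no discernible difference in heat acclimatization status".

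Section 4.2 specifies a "restricted maximum likelihood (REML)-based linear mixed model, accounting for repeated measures", with fixed effects given as "including a term for hydration status (euhydrated, dehydrated), a term for condition (no fan use, fan use), and interaction term". The same model serves all six outcomes. Participants with missing conditions are kept and all available data are used.

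Section 4.1 sets the number: "we plan to recruit at least 16 young healthy participants".

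**The concern.** The design controls visit position, and the analysis as written then leaves it out. Four 3-hour exposures at 39°C within three weeks could produce some trend across visits, through partial adaptation or growing familiarity with the chamber, the rectal probe and the scales. Three of the six outcomes in section 2.4 (thermal sensation, thermal discomfort, thirst) are self-ratings, where familiarity is plausible.

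The primary objective in section 2.1 asks whether dehydration modifies the fan effect, which is the hydration-by-fan interaction. Section 3.1 justifies the crossover by its low within-person variation. A trend left in the residual gives some of that advantage away. It could contribute to a non-significant interaction being read as evidence that dehydration does not change how well fans work.

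**Working it through.** **The plan's own figure.** Section 4.1 gives alpha 0.05, beta 0.1 and a standardised effect of 0.78. A one-sided paired t-test with these inputs needs n = 16 (power 90.8%). A two-sided paired t-test needs n = 20, and has 83.0% power at n = 16. Sidedness is not stated. The 0.78 describes a euhydrated-versus-dehydrated difference, not the interaction, so it does not fix an effect size for this check.

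**Inputs.** From the protocol: 16 participants, four visits, balanced Latin square, fixed effects hydration, fan and interaction. Assumed:
- within-person residual SD σ = 1, with compound symmetry (participant intercept);
- linear drift totalling D from visit 1 to visit 4, with D from 0 to 2 SD;
- an interaction (difference of differences) of 1.6 SD;
- two-sided alpha 0.05.

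**Degrees of freedom.** 16 × 4 = 64 observations. Without visit: 64 − 16 − 3 = 45. With visit: 45 − 3 = 42.

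**Bias with complete data.** With 16 participants over four sequences, each condition falls four times at each visit position. Visit is orthogonal to all three contrasts, so omitting it leaves the estimates unbiased.

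**Residual inflation.** The expected residual mean square without visit, relative to σ², is 1 + 16·Σ(π_j − mean)²/45. For linear drift the visit effects are −D/2, −D/6, D/6 and D/2, so the sum of squares is D²(1/4 + 1/36 + 1/36 + 1/4) = 5D²/9. At D = 1 this gives 1 + 16 × 0.5556/45 = 1.198, and √1.198 = 1.094 for the SE.

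**Power with no drift.** The SE of the interaction is √(4σ²/16) = 0.50, so the noncentrality is 1.6/0.50 = 3.2. Power is 87.9% on 45 df and 87.8% on 42 df.

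**Power with drift.** Simulation, 40,000 trials per setting for the sizes and powers (rounded):

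| Total drift (SD) | Residual ratio | SE ratio | Test size, no visit term | Power, no visit term | Power, visit term |
|---|---|---|---|---|---|
| 0 | 1.00 | 1.00 | 5% | 88% | 88% |
| 0.25 | 1.01 | 1.01 | 5% | 88% | 88% |
| 0.5 | 1.05 | 1.02 | 4.5–5% | 87% | 88% |
| 1 | 1.20 | 1.09 | 3% | 84% | 88% |
| 1.5 | 1.44 | 1.20 | 2% | 78% | 88% |
| 2 | 1.79 | 1.34 | 1% | 69–70% | 88% |

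The true sampling SD of the interaction estimate stays at 0.50 in every row. Only the estimated SE grows, which is why the test becomes conservative.

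**Sensitivity to the effect size.** With an interaction of 1.56 SD (0.78 in units of the SD of a participant's interaction contrast, which is 2σ), power without the term is about 86%, 86%, 85%, 82%, 75% and 66% at the same drifts. With the term it is about 86% throughout.

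**Loss of balance.** Take 18 enrolled (a hypothetical number) and D = 1. The first 16 contribute no bias. The two extra participants contribute their own drift contrasts, each 0, ±2/3 or ±4/3, and the total is divided by 18. Over all pairs of different sequences and all labellings of the conditions, the absolute bias is 0, 0.04 or 0.11 SD, mean 0.03. The maximum is (4/3 + 2/3)/18 = 0.11, against an SE of 2/√18 = 0.47, so under a quarter of an SE. Missing visits break the balance in the same way; the size depends on which visits are lost. A visit term removes the bias in both cases.

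**The case against.** The strongest reply is that the harm rests on a drift size that appears nowhere in the protocol. Up to about 0.5 SD the loss is about one percentage point, and the larger losses need a drift of 1 SD or more. This stands, and is why the point is conditional.

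The protocol also acts on drift by design, through the spacing, the three-week window and the counterbalancing. These make a large acclimatization trend less likely. They do not rule it out, they are not checked in the analysis, and they do not address familiarisation.

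A reader might infer that the planned analysis is biased or invalid. It is not: for complete balanced data the estimates are unbiased, and the error is on the conservative side, with no added false-positive risk. The planned 16 is a multiple of four, so bias enters only if sequences fill unequally or visits are lost, and then it is small.

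A reader might also infer that the trial is already short of power for its interaction. The protocol gives no interaction effect size, so that is not shown. The 1.6 SD used here is illustrative.

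Finally, the wording of section 4.2 is not strictly exhaustive, the covariance structure is left open, and a statistical analysis plan not at hand might add a visit term. Under an unstructured covariance the figures would change with how conditions are assigned in the square. Even so, section 4.2 sets out its fixed effects specifically, without the factor that section 3.1 controls.

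**Conclusion.** The omission is real and its consequence conditional. Without a visit term, drift across the four exposures enters the residual and makes the tests conservative. Under the stated assumptions (linear drift, compound symmetry, 16 complete participants, a 1.6 SD interaction), the power loss is about 1 point or less up to 0.5 SD, about 4 points at 1 SD, about 10 at 1.5 SD and about 18 at 2 SD. The protocol does not tell us where in that range the trial lies, so the losses at 1.5 to 2 SD should not be read as expected. Bias is a secondary matter, absent in complete balanced data and at most 0.11 SD in the 18-participant example. The case for changing the model is that the safeguard is almost free, not that the planned analysis is wrong.

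**What to change.** In Protocol section 4.2, add visit number (1 to 4, categorical) as a fixed effect in the model for every outcome, keeping participant as the repeated or random subject. State the covariance structure at the same time, since the effect of the term depends on it.

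The cost is 3 of 45 residual degrees of freedom. With no drift, power changes by about 0.1 point (87.9% to 87.8%). Visit number is already known for each exposure, so nothing in trial conduct or data collection changes.
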